### Participant timeline {13}

The participant flow chart can be seen in Fig. 1 and the overall participant timeline in Fig. 2. There will be a rolling recruitment and enrolment strategy, with recruitment efforts ending when the full sample of caregiver-adolescent dyads have been successfully identified and enrolled in the study; we anticipate a timeline of 4–6 months to reach the intended sample size. The first post-intervention data collection will take place around week 16, following participant engagement in the intervention. Further follow-up surveys will be conducted approximately 16 months after beginning the apps. At follow-up, participants will be asked for consent to contact them again in the future, in case of longer-term follow-up.

**Fig. 1 Fig1:**
[figure not shown]
Participant flow chart

**Fig. 2 Fig2:**
[figure not shown]
Schedule of enrolment, interventions, and assessments

### Sample size {14}

The study will recruit approximately 2400 caregiver-adolescent dyads (i.e. 2400 caregivers and 2400 adolescents) to take part in the RCT; of these, between 40 and 60 caregivers and between 20 and 30 adolescents will also participate in an individual post-programme qualitative interview. The sample size was determined by power calculations from the pilot study, using multilevel Poisson regression.

modelling. These suggest that if the outcome scale generates a control group mean of 4 and an effect size of 0.95, and accounting for attrition in both the trial and the programme, to get 80% power a minimum of 80 clusters with 30 families in each cluster is required (i.e. 2400 caregiver-adolescent dyads). Semi-structured qualitative interviews will also be conducted with 10 staff responsible for programme delivery at each of the implementing organisations. Adolescent siblings or co-residents in the household in an estimated 50% of households will be assessed at endline only.

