### Trial design {8}

This is a two-arm, pragmatic, cluster-randomised controlled trial with assessments at baseline, 1 month post-intervention and 12 months post-intervention. Randomisation will be performed at the cluster level with a 1:1 allocation ratio.

A total of 80 urban and peri-urban clusters in Mwanza, Tanzania, containing on average 30 caregiver-adolescent dyads each, will be randomised to two parallel arms. Caregivers in intervention sites will receive a basic smartphone, which will be loaded with the Kiswahili version of ParentApp and will be invited to join a WhatsApp group to discuss and share solutions as they use the app. Caregivers in control sites will also receive a basic smartphone, which will be loaded with a Kiswahili app giving water, sanitation, and hygiene (WASH) information and WhatsApp.

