## Statistical methods

### Statistical methods for primary and secondary outcomes {20a}

Quantitative data will be cleaned and analysed in R, R studio and Stata. The primary method of analysis will be via a three-level model with adjustment for person-level characteristics and multiple imputation. In this three-level model, measurement waves are nested within a person, and this is nested within a village or residential area (i.e. cluster). Each regression will include at level 3, a term for intervention allocation, the variable used to stratify randomisation, percentage of male caregivers in the village sample, and, as appropriate, the mean of any additional level 2 covariates; at level 2, variables for individual demographic characteristics (e.g. gender, age, disability, caregiver-child relationship) centred at the overall sample mean; and at level 1, a variable for categorical time and interactions between intervention allocation and categorical time (i.e. the test of intervention effectiveness). In situations where more than one caregiver or adolescent is recruited from a family, a clustered standard error structure will be implemented on level 2. The regression link function will be based on consideration of outcome distributions. For example, where outcomes are binary, a logit link will be used; where outcomes take on integer values from 0 and are count-distributed, then a Poisson distribution will be used. We will also produce unadjusted multiply imputed estimates for each outcome, including only terms for intervention, stratification, time, and intervention by time; and unadjusted unimputed estimates for each outcome, following the same specification.

The *p*-value threshold will be 0.05 for all pre-specified analyses. However, due to multiple comparisons planned for exploratory analyses, a sharpened *q*-value will be used with respect to all exploratory analyses to adjust the *p*-value threshold for statistical significance to reduce the likelihood of false positives. False discovery will be controlled using a testing hierarchy.

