The significance of the fixed effects in the model will be evaluated using Wald tests, which assess whether the regression coefficients are significantly different from zero. Overall, intervention effectiveness for a given outcome will also be evaluated via a likelihood ratio test comparing models with intervention by time interactions with models without intervention by time interactions. For random effects, the intracluster correlation coefficient (ICC) may also be used to evaluate the proportion of variance in the outcome variable that is due to variation in the higher-level units. Because ICC is also dependent on variable scale where variables are e.g. binary or Poisson distributed, we will also estimate the median incidence rate ratio or odds ratio as appropriate.

Where variables are approximately normally distributed with respect to covariates, mean differences will be used. Where variables are Poisson-distributed, incidence rate ratios (IRRs), which represent the ratio of the incidence rate or frequency of the outcome in one group compared to another group, will be calculated. The advantage of using IRRs is that they allow for the comparison of rates, frequencies or ratios of means across different time points or groups, while controlling for other covariates. Where outcomes are binary or ordinal, odds ratios will be estimated.

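### If the effect size of 0.95 is an incidence rate ratio tested two-sided at one follow-up, 80 clusters of 30 give at most about 70% power, not the stated 80%

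*Protocol article*

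**What the plan says.** The Sample size section of the protocol article reports: "The sample size was determined by power calculations from the pilot study, using multilevel Poisson regression". It gives "a control group mean of 4 and an effect size of 0.95", adds that the figure was reached while "accounting for attrition in both the trial and the programme", and concludes that "to get 80% power a minimum of 80 clusters with 30 families in each cluster is required". That makes 2400 dyads. Trial design {8} adds: "Randomisation will be performed at the cluster level with a 1:1 allocation ratio", so there are 40 clusters and 1200 dyads per arm.

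The statistical methods section {20a} sets a p-value threshold of 0.05 for pre-specified analyses. It describes Wald tests of "whether the regression coefficients are significantly different from zero", which implies two-sided testing, although sidedness is never stated. For count outcomes it names the effect measure: "Where variables are Poisson-distributed, incidence rate ratios (IRRs), which represent the ratio of the incidence rate". It identifies the contrast that carries the effectiveness claim as "interactions between intervention allocation and categorical time (i.e. the test of intervention effectiveness".

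The article does not say whether 0.95 is a ratio or a difference, or to which time point and contrast the power refers.

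**The concern.** A sample size statement should return its own power figure when its inputs are put back in. Here the model is Poisson and the article's effect measure for Poisson outcomes is the IRR, so 0.95 most naturally means a 5% lower mean count. That is a small effect. With a mean of 4, Poisson noise alone appears too large for 1200 dyads per arm to detect it with 80% power, before the clustering and attrition that the text says were covered.

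What is at stake is how a non-significant result is read. Interim analyses {21b} says that 1-month and 12-month results will be shared because the national government has asked to scale up the programme. If the stated power is too high for the stated effect, a null result would look more informative than it is.

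**Working it through.** **Inputs from the article.** Control mean 4; effect 0.95; 80 clusters of 30, allocated 1:1, so 1200 per arm; threshold 0.05. **Assumed:** 0.95 is an IRR (4.0 against 3.8), the test is two-sided, and variance is pure Poisson.

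**1. The stated 80%, one follow-up, no clustering, no attrition.**
- SE(log IRR) = √[1/(1200 × 4) + 1/(1200 × 3.8)] = √(1/4800 + 1/4560) = 0.0207
- |ln 0.95| = 0.0513, so z = 0.0513/0.0207 = 2.48
- Power = Φ(2.48 − 1.96) = 69.9% (69.7% in a Poisson simulation of 200,000 runs)

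The 80% is not reproduced. Covariates cannot remove Poisson noise, so this is a ceiling for a single-follow-up comparison. To show the direction, with assumed values because the article gives none: 10% attrition alone gives 65.3%, 20% gives 60.2%, and an intracluster correlation (ICC) of 0.01 with full follow-up gives 58.9%.

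**2. What 80% would need under the same ideal conditions.**
- n per arm = (1.96 + 0.84)² × (1/4 + 1/3.8)/0.0513² ≈ 1531
- 1531/30 = 51.03, so just over 51 clusters per arm against 40 planned
- With 1200 per arm, the IRR detectable with 80% power is about 0.944

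**3. The planned contrast (change from baseline, by arm).**
- Baseline adds 2/4800 to the variance: 1/4800 + 1/4560 + 2/4800 = 0.000844, so SE = 0.0291
- z = 0.0513/0.0291 = 1.77; power = Φ(1.77 − 1.96) ≈ 42%
- The joint 2-df test over both follow-ups, with the same IRR at each, gives about 43%

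No clustering penalty is applied here, because stable differences between clusters largely cancel from a change contrast.

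**4. Routes that do return about 80% with an IRR of 0.95.**
- One-sided 5%, no clustering, no attrition: Φ(2.48 − 1.645) = 79.8%. It falls to 76.1% with 10% attrition and to 70.5% with ICC 0.01.
- Both follow-ups pooled, no attrition, no between-person variance, between-cluster coefficient of variation (CV) 0.05: variance = 0.000428/2 + 2 × 0.05²/40 = 0.000339, SE = 0.0184, z = 2.79, power 79.6%. With no clustering the pooled figure is 94%.

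**5. 0.95 as an absolute difference (4 against 3.05).**
- Pure Poisson: SE = √[(4 + 3.05)/1200] = 0.0766, z = 12.4, power about 100%. A design effect of about 19.6 (ICC about 0.64) would be needed to bring this down to 80%.
- SD 6, ICC 0.03, no attrition: design effect 1 + 29 × 0.03 = 1.87; SE = √(2 × 36/1200 × 1.87) = 0.335; z = 2.84; power 81%. An SD of 6 means a variance of 36, nine times the Poisson value of 4.
- SD 5, ICC 0.05, 30% attrition (21 per cluster, 840 per arm): design effect 2.0; SE = 0.345; power 79%.

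**The case against.** The strongest defence is that the article never labels 0.95, so the shortfall rests on inferred metric, sidedness and time point. That stands, and it is why the conclusion is conditional. A reader might infer that 80% is impossible on any reading. The documents do not support this. With a mean difference of 0.95, step 5 shows 80% within reach once the outcome is much more variable than Poisson. Allowing for programme attrition could also mean that the effect was diluted: a difference cut by 30% to 0.665, with SD 4, ICC 0.03 and 15–20% attrition, gives 80–81%. These are assumed values, but the pilot's variance figures are not shown and cannot be ruled out.

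A second defence is that a journal article condenses a fuller document, so an unprinted ICC, dispersion or attrition rate is not a fault. That also stands, but it does not rescue the IRR reading. Any non-negative ICC and any attrition rate leave single-follow-up power at or below 69.9%.

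The routes in step 4 do not fit the text. The one-sided match needs no clustering and no attrition, whereas the article describes a multilevel model with attrition allowed for and tests of difference from zero. Pooling the follow-ups also has to leave out attrition to match, and it is not the planned analysis, which treats time as categorical and reports 1 month and 12 months separately. That the 80% came from a one-sided calculation would be a guess.

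**Conclusion.** The concern holds conditionally. If 0.95 is an IRR and the test is two-sided at 5% at one follow-up, power is at most 69.9%, about ten percentage points below the stated figure before clustering or attrition. For the intervention-by-time contrast it is about 42% under ideal Poisson conditions. The IRR reading is the natural one from the Poisson model and the article's own effect measure, but it is an inference. If 0.95 is an absolute difference, the 80% cannot be confirmed from what is printed: power is near 100% under near-Poisson variance, and 80% requires large unstated overdispersion or clustering.

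A reader might go further and quote a realistic power well below 70%, or a specific detectable IRR with clustering included. The documents give no ICC, between-cluster CV, dispersion or attrition rate to support such figures. Clustering penalties worked out for a single time point also do not carry over to the change-from-baseline contrast. How government would read a null result is likewise a matter of judgement, not something the article states.

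**What to change.** Keep the 80 clusters. In the sample size statement, name the metric of 0.95 and give the sidedness, the time point and the contrast to which the power refers. Recompute for the planned intervention-by-time test, using the pilot's own between-cluster variance, dispersion and attrition, and print the result with those inputs.

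If 0.95 is an IRR, either replace the 80% with the recomputed power (no more than about 70% for a single-follow-up comparison) or state the IRR detectable with 80% power (no closer to 1 than about 0.944 for that comparison). If 0.95 is a mean difference, say so and give the SD and ICC that lead to 80%.

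The cost is one recalculation and a change of wording in the protocol or analysis plan. It needs no extra clusters and no change to the analysis, though the stated power may become less favourable.

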### Recruitment {15}

Recruitment follows pragmatic trial principles of closely approximating government scale-up. We will work via established partnerships with UNICEF and the Tanzanian government, through NIMR, and local implementing partner organisation, ICS. Recruitment of caregiver-adolescent dyads will involve a range of strategies, including recruitment through existing groups (such as farmer’s groups), dissemination of posters and flyers in the community, word-of-mouth referral and/or online recruitment methods. Approval will first be sought from local community and political leaders before recruitment activities commence, and they will be closely involved in community mapping and recruitment efforts in their respective communities to identify caregivers who meet the recruitment criteria.

## Assignment of interventions: allocation

### Sequence generation {16a}

The study will use a stratified cluster randomisation procedure. Cluster randomisation will be stratified by cluster location (urban and peri-urban) and use a block size of six clusters. The stratum will be used in the analysis and included as a pre-planned covariate, the percentage of males in the cluster.

### Concealment mechanism {16b}

The Trial Statistician will generate 100 possible allocations for each block, where each block is composed of sites from the same stratum (i.e. urban, or peri-urban). One allocation from the possible allocations within a given block will be chosen at random during a community randomisation meeting using a participatory approach. The identities of the sub wards/clusters will be concealed to the statistician calculating the randomisation.

### Implementation {16c}

The fieldwork team will collect baseline data in blocks of six clusters that are all either (a) urban or (b) peri-urban. Once baseline data has been collected for a block of six clusters, the fieldwork team will hold a collective randomisation ceremony to allocate the sites in that block (i.e. randomisation is done as baseline data collection is completed for the four sites in a block). This will be conducted by asking a community participant or leader to randomly select a number, e.g. by picking a slip of numbered paper from a hat.

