## Assignment of interventions: blinding

### Who will be blinded {17a}

The implementing partner will notify the participating families of their allocation status after baseline data collection in their cluster is complete to assure that participants are blind to allocation during the baseline assessments. The allocation status of participating families in other clusters will be concealed from participants, thus reducing the potential for contamination. Based on prior trials of parenting programmes, we do not anticipate that blinding will be possible for research staff after baseline data collection as families usually mention their participation in the intervention or control programme. Similarly, of course, participants cannot be blind to their own treatment condition. However, the data analysts will be blinded from condition assignment during analysis.

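### The block size is given as both six and four clusters, and the planned models leave out the blocks, which makes the test conservative if blocks change differently over time

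*Protocol article*

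**What the plan says.** Trial design {8} gives "A total of 80 urban and peri-urban clusters in Mwanza, Tanzania", and adds: "Randomisation will be performed at the cluster level with a 1:1 allocation ratio".

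Sequence generation {16a} stratifies by urban or peri-urban location and will "use a block size of six clusters". Implementation {16c} repeats six: baseline is collected in blocks of six clusters from one stratum, and a ceremony to allocate the block follows once its baseline is done. The bracket that explains this sentence then says "randomisation is done as baseline data collection is completed for the four sites in a block".

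Concealment mechanism {16b} says: "The Trial Statistician will generate 100 possible allocations for each block". One of these is picked at random at the community meeting. The section does not say whether the 100 are all different.

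In Statistical methods {20a}, the cluster-level terms of the main model are allocation, "the variable used to stratify randomisation", the percentage of male caregivers and, where needed, cluster means of person-level covariates. The unadjusted models carry only intervention, stratification, time and intervention by time. No model listed has a block term.

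**The concern.** The block size is an operating rule of the randomisation. It decides when a ceremony may be held and how many sites it covers. A reader who wants to check that baseline came before allocation in each cluster needs one number, and the article gives two.

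The second part concerns the analysis. Baseline is collected block by block, and Trial status places the baseline interviews between April and the end of September 2023. A block therefore marks a stretch of calendar time as well as a randomisation unit. If outcomes change differently in clusters enrolled early and late, that variation is balanced between arms by design. A model without blocks still counts it as error. At stake is precision, in a trial whose Sample size {14} section says that "a minimum of 80 clusters with 30 families in each cluster is required (i.e. 2400 caregiver-adolescent dyads" for 80% power.

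**Working it through.** **Inputs.** 80 clusters and 1:1 allocation ({8}); 30 dyads per cluster ({14}); block size six ({16a}, {16c}) or four ({16c}); 100 listed allocations per block ({16b}); model terms ({20a}). The numbers of urban and peri-urban clusters are not given. The total reproduces: 80 × 30 = 2400 dyads.

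**1. Which block size fits?**
- Six: 80 = 13 × 6 + 2. For a split into u urban and 80 − u peri-urban clusters, the possible remainders on division by six are (0,2), (1,1), (2,0), (3,5), (4,4) and (5,3). The pair (0,0) does not occur, so at least one block is short.
- Four: 80 = 20 × 4, with none left over when both stratum totals are multiples of four.

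The count of mentions favours six and the arithmetic favours four, so the text does not settle it.

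**2. The list of 100.** A balanced block of six has C(6,3) = 20 allocations (a block of four has C(4,2) = 6). Even without balance only 2^6 = 64 exist, so a list of 100 must repeat some. Since 100 = 5 × 20, listing each balanced allocation five times is exactly uniform. If the 100 are instead drawn at random with replacement from the 20, a list holds 19.9 distinct allocations on average. A site's chance of intervention is 0.50 over all lists. Given one particular list it lies between about 0.40 and 0.60 (central 95%).

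**3. Leaving blocks out.** The test of effectiveness is the intervention-by-time interaction, so the relevant quantity is the change in each cluster from baseline. Let r be the share of the cluster-level variance of that change that lies between blocks. The document gives no value for r, so a range is assumed.

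With equal allocation inside blocks, the effect estimate varies only with the within-block part, proportional to 1 − r. An analysis without blocks uses the whole variance, so its standard error is too large by roughly 1/√(1 − r).

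Type I error was simulated at cluster level, with 13 blocks of six and one of two, and 10,000 runs per setting:

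| r (assumed) | SE too large by the factor 1/√(1 − r) | Type I error, no block term | Type I error, block term |
|---|---|---|---|
| 0 | 1.00 | 0.051 | 0.051 |
| 0.10 | 1/√0.90 = 1.05 | 0.037 | 0.047 |
| 0.25 | 1/√0.75 = 1.15 | 0.022 | 0.046 |
| 0.50 | 1/√0.50 = 1.41 | 0.009 | 0.052 |

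**4. Which block term helps?** In a linear model with complete data, a constant block effect enters every wave alike and cancels from the change. Adding block as a main effect alone therefore leaves the intervention-by-time estimate and its standard error as they were. Block-by-time removes the variation in step 3.

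**5. Cost in degrees of freedom.** Fourteen blocks nested in two strata add 14 − 2 = 12 terms per time contrast. At cluster level, 80 − 2 strata − 1 for treatment leaves 77. With fixed block terms, 80 − 14 − 1 = 65 remain. With 20 blocks of four, 80 − 20 − 1 = 59 remain. Random effects cost less.

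**The case against.** The strongest reply is that the bracket in {16c} only restates the sentence it sits in. Whatever the block size, it refers to all sites of the block, so every cluster finishes baseline before allocation. That stands. A reader might infer that a six-cluster allocation is drawn after four sites, so that two clusters in every six (26 in 13 full blocks, or 780 dyads) are allocated before baseline. No section describes that hybrid. Who will be blinded {17a} also has families told only once baseline in their own cluster is finished, so that "participants are blind to allocation during the baseline assessments". The article does not support a claim of broken concealment or broken baseline blinding.

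A reader might also infer that the 1:1 ratio fails, because 80 is not a multiple of six or because 100 allocations exceed the 20 that exist. Neither follows. A short last block is routine, its handling may sit in the full protocol, and 40:40 can be reached with balanced short blocks when both stratum totals are even. A list with repeats is workable, nothing suggests that it contains unbalanced allocations, and cluster identities are hidden from the statistician who makes it.

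Last, leaving blocks out can be defended as a modelling choice, since it causes neither bias nor false positives. That is correct. What remains is a possible loss of power that is cheap to avoid.

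**Conclusion.** One contradiction stands: the block size is six in {16a} and in most of {16c}, and four in the bracket of {16c}. It needs correcting against the randomisation records. It does not show that anything was done wrongly.

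The missing block terms are a matter of efficiency. With no difference between blocks in their change over time, nothing is lost. At assumed shares of 10% to 50%, the standard error is about 5% to 41% too large and the true type I error is about 0.037 to 0.009 instead of 0.05. These figures rest on assumed variance shares, equal allocation within blocks, a cluster-level linear approximation and 14 blocks. Models with a logit or Poisson link will behave similarly but not identically.

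The list of 100 is loosely described and not inconsistent with the design.

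**What to change.** - Correct {16c} or {16a} to the block size that was used. From the randomisation log, report the size of each block, including any short one, and confirm that all its clusters had completed baseline before the draw.
- Add block (nested in stratum) and block by time to the {20a} models, preferably as random effects. A block main effect alone is not enough. Set this down before the analysts see outcomes by arm.
- State that the list of 100 holds each of the 20 balanced allocations of a six-cluster block equally often (five times). If the size proves to be four, give the matching statement for its six balanced allocations.

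The first and third items cost a line of text and a short check of the log. The second costs at most about 12 of 77 cluster degrees of freedom with 14 blocks, or 18 with 20 blocks, and less with random effects. No new data are needed.
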